#### **10.7.3. According-to-Protocol (ATP) cohort for analysis of immunogenicity**

The ATP cohort for analysis of immunogenicity will include all evaluable subjects (i.e. those meeting all eligibility criteria, complying with the procedures defined in the protocol, with no elimination criteria during the study) for whom data concerning immunogenicity endpoint measures are available.

#### **10.7.4. According-to-Protocol (ATP) cohort for analysis of efficacy**

The ATP cohort for analysis of efficacy will include all evaluable subjects (i.e. those meeting all eligibility criteria, complying with the procedures defined in the protocol, with no elimination criteria during the study) for whom data concerning efficacy endpoint measures are available.

### **10.8. Derived and transformed data**

- Seroprotection rate for anti-HBsAg is defined as the percentage of subjects with antibody titers greater than or equal to an established cut-off (anti-HBsAg  $\geq 10$  mIU/mL).
- A subject seropositive for anti-CS antibody is a subject whose antibody titer is greater than or equal to the cut-off value (anti-CS  $\geq 0.5$  EU/mL).
- The Geometric Mean Titers (GMTs) calculations are performed by taking the anti-log of the mean of the log10 titer transformations. Antibody titers below the cut-off of the assay will be given an arbitrary value of half the cut-off for the purpose of GMT calculation.

For a given subject and a given immunogenicity measurement, missing or non-evaluable measurements will not be replaced. Therefore, an analysis will exclude subjects with missing or non-evaluable measurements.

### **10.9. Statistical methods for Vaccine Efficacy endpoints**

#### **10.9.1. Time to event analyses**

For time to endpoints (time to first or only episode of *P. falciparum* malaria), the incidence of episodes (episodes/person years at risk) for each group will be presented. Kaplan-Meier curves for both groups will be shown. The distribution of the “time to” will be compared with the Wilcoxon test (if efficacy varies with time) or the Log-rank test (if it does not). Vaccine Efficacy will be assessed using Cox regression models. Vaccine

efficacy is defined as 1 *minus* R where R is the hazard ratio of the RTS,S/AS01E group versus the Control group (with 95% CI). Crude and adjusted estimates for covariates (possible covariates include: study center, bed-net use, geographical area and distance from health center) will be presented.

Cox regression assumes proportional hazards throughout the follow-up period. This assumption will be checked by plotting per group the log of the cumulative hazard against the log of time. Under the assumption of proportionality of the hazard, both curves should be parallel. A test based on the Schoenfeld residuals will be performed.

If there is strong evidence that the hazard is not constant over the surveillance period, then alternative approaches to analyze the data may be examined according to the following:

- Cox regression models with time varying covariates, using fractional polynomials to identify the function of the time that best fits. The following functions of the time will be explored : -2, -1, -1/2, log, identity, 1/2, 2, 3. The Akaike's criterion and the Schwarz Bayesian criterion will be explored.
- Accelerated failure time (AFT) models using 'Generalized Gamma', 'Standard Gamma', 'log-normal', 'weibull' and 'exponential' distributions.

In order to assess the goodness-of-fit of these models, a graphical representation of the expected survival curve against the observed using the Kaplan-Meier methodology will be presented. Where appropriate, likelihood ratio tests will be carried out to investigate the goodness-of-fit of the different models if appropriate.

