### **1.6.4. Rationale for study extension**

*Vaccinations began in March 2007. A series of logistic factors, including a change of supplier for the rabies control vaccine leading to interruption in delivery of the study vaccine, and lower than expected recruitment rates resulted in a variable delay of vaccination, such that surveillance post Dose 3 began in May 2007 for some children, but in October 2007 for others. 12 months of surveillance post Dose 3 are planned according per protocol, so children will finish surveillance in the period June 2008-October 2008.*

*The high malaria transmission season is June-October in Kilifi and March-August in Korogwe. In this amendment dated April 2008, we propose to continue active and passive case detection in all children until the end of the transmission season. This will result in a variable length of follow up, but all children will end surveillance on the same date in each site (October 2008 in Kilifi, September 2008 in Korogwe). Surveillance is therefore extended through the transmission season for all subjects and is likely to produce an increase in power.*

*There will be two additional visits. The first visit (Clinic Visit 8) at the start will be to request informed consent. The second visit (Clinic Visit 9) at the close of study will allow to assess safety at the final time-point, and to obtain a cross-sectional bleed in order to study parasite prevalence at the end of the malaria transmission season. The duration of protection may be linked to the duration of immunogenicity, and so serum will be used from this final time-point to measure vaccine-induced antibodies to the circumsporozoite antigen (CS).*

*Amended 17 April 2008*

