**6.4. Treatment allocation and randomization****6.4.1. Randomization of supplies**

There will be a separate randomization list supplied to each site with no overlap of Treatment Numbers. The randomization list will be generated at GSK Biologicals, Rixensart, using a standard SAS (Statistical Analysis System) program and will be used to number the vaccines.

In this randomization process, volunteers will be allocated randomly to one of two study groups defining which vaccine should be given (i.e. RTS,S/AS01E or Rabies vaccine). Each group will have the same number of subjects.

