## **10.6. Estimated sample size**

### **10.6.1. Power Calculations**

The final analysis is projected to occur after the completion of 4 months of surveillance, at which time it is assumed that 36% of children in the control group will have been affected by a malaria episode. Assuming a true vaccine efficacy of 30% and an attack rate of 36% in controls (corresponding to an attack rate of 25.2% in vaccinees), a sample size of 400 evaluable subjects per group has 90% power to detect a difference between groups using a 2-sided Fisher exact test at 5% significance level. The final analysis is projected to occur after the completion of 4 months of surveillance, at which time it is assumed that 36% of children in the control group will have been affected by a malaria episode. However, in the event that malaria rates are lower in the year of the study, the unblinding and analysis will be delayed until approximately 245 children have experienced an episode ( $400 \times 36\% + 400 \times 25.2\% = 245$ ). This analysis will also have 90% power.

The assumption of 36% attack rate in controls is based on epidemiological data collected at the two sites. In Kilifi the proportion of children aged 12 to 18 months olds affected by a malaria episode using the same ACD methodology as proposed in this document over the same time frame in 2005 was 37% (personal communication [name]). In Korogwe the case rate was 34% determined in children aged 5 to 17 months in Mkokola village (10 km from Korogwe) by Passive Case Detection at village level (personal communication [name], [name]).

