### 10.9.3. Cross-sectional analyses

Hemoglobin mean and standard deviation will be presented (following cross-sectional visit at Clinic Visit 6 and Month 14 **and Clinic Visit 9**) and 95% confidence intervals will be calculated. The effect of the group will be evaluated using a non-parametric Wilcoxon test.

For the assessment of the parasite density at following cross-sectional visit at Clinic Visits 6 and 7 **and 9**, a 2x2 table presenting the frequency of positive and negative will be

presented. The effect of the group will be evaluated using the Fisher exact test. The Geometric mean of those positive in each group will be calculated. Difference in geometric mean and 95% CI will be estimated. The effect of the group will be evaluated using a non-parametric Wilcoxon test.

*Amended 17 April 2008*

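### Allocation is stratified by site, but the named log-rank/Wilcoxon and Fisher tests and the crude Cox estimate carry no site term, and no vaccine efficacy estimate is named as primary

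*Protocol*

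**What the plan says.** On allocation, Section 6.4.1 states: "There will be a separate randomization list supplied to each site with no overlap of Treatment Numbers". Section 6.4.2 has children randomised in the order they present, from the list for their site. Allocation is therefore stratified by site.

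On the time-to-event analysis, Section 10.9.1 compares the groups with a Wilcoxon test if efficacy varies with time and a log-rank test if it does not. No stratification is stated for either. Vaccine efficacy is one minus the Cox hazard ratio, and "Crude and adjusted estimates for covariates (possible covariates include: study center, bed-net use, geographical area and distance from health center) will be presented". Section 10.9.5 lists study center among the covariates to be collected and leaves the set used for adjustment to the Report and Analysis Plan, which was not available for this review. Nothing says whether the crude or the adjusted estimate is primary.

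On the surveys, Section 10.9.3 sets out a two-by-two table of parasite-positive and parasite-negative children by group: "The effect of the group will be evaluated using the Fisher exact test".

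On the sites, Section 10.6.1 gives planning attack rates of 37% for Kilifi and 34% for Korogwe. Section 1.6.4 states: "The high malaria transmission season is June-October in Kilifi and March-August in Korogwe".

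**The concern.** When two strata with different risks are pooled, the higher-risk children leave the risk set sooner, and they leave faster in the control arm. The pooled hazard ratio is then pulled towards 1 even though the within-site ratio is the same at both sites. The unstratified log-rank test also loses power, because between-site variation that the design has balanced stays in its variance. Stratifying the analysis by the factor used to randomise removes both effects.

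At stake are some power for the main comparison and a small understatement of vaccine efficacy. There is also an open choice of headline result: with a crude and an adjusted estimate both presented and neither ranked, the protocol does not settle which one answers the primary objective.

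**Working it through.** **The plan's own figure.** Section 10.6.1 plans on "Assuming a true vaccine efficacy of 30% and an attack rate of 36% in controls", so 0.36 × 0.70 = 25.2% in vaccinees. For a two-sided Fisher test at the 5% level it states that "a sample size of 400 evaluable subjects per group has 90% power to detect a difference between groups". Exact enumeration of the two-sided Fisher test at 400 per group gives 90.2%. Expected events are 400 × 0.36 + 400 × 0.252 = 244.8, matching the rule that analysis be "delayed until approximately 245 children have experienced an episode". The stated figures reproduce.

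**Effect sizes.** Attack rates of 36% and 25.2% imply a hazard ratio of ln(1 − 0.252)/ln(1 − 0.36) = 0.651. A 30% efficacy on the Cox scale, which is how Section 10.9.1 defines efficacy, is a hazard ratio of 0.70. Both are used below.

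**Assumptions.**
- Half the children are at each site (Table 6 counts 445 of 890 at KEMRI), giving 200 per arm per site.
- Hazards are constant within site over the follow-up period, scaled to length 1.
- The hazard ratio HR is the same at both sites.
- The contrasts 50%/22% and 60%/12% are assumed. Each averages 36%, the planned control rate.

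**Method.** The control hazard at site j is λj = −ln(1 − pj). In arm a (hazard multiplier ha = 1 for control, HR for vaccine), the number at risk is Sa(t) = Σj 200·exp(−λj·ha·t), with events dEa = Σj 200·λj·ha·exp(−λj·ha·t) dt.
- Crude Cox limit: b solves ∫[dE1 − (dE0 + dE1)·S1·e^b/(S0 + S1·e^b)] = 0, and crude efficacy is 1 − e^b.
- Unstratified log-rank: with π = S1/(S0 + S1), U = ∫[dE1 − (dE0 + dE1)π] and V = ∫(dE0 + dE1)π(1 − π). Power = Φ(|U|/√V − 1.96).
- Stratified log-rank: compute U and V within each site and add them.

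The hazard contrasts are 0.462/0.416 = 1.11 for 37%/34%, 0.693/0.248 = 2.79 for 50%/22%, and 0.916/0.128 = 7.17 for 60%/12%.

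| Control rates by site | HR | Power, unstratified | Power, stratified | True VE | Crude VE |
|---|---|---|---|---|---|
| 37%/34% (protocol) | 0.70 | 79.7% | 79.7% | 30.0% | 29.99% |
| 50%/22% (assumed) | 0.70 | 77.1% | 80.6% | 30.0% | 28.9% |
| 60%/12% (assumed) | 0.70 | 70.0% | 81.1% | 30.0% | 26.8% |
| 37%/34% (protocol) | 0.651 | 91.1% | 91.2% | 34.9% | 34.9% |
| 50%/22% (assumed) | 0.651 | 89.5% | 91.8% | 34.9% | 33.8% |
| 60%/12% (assumed) | 0.651 | 84.3% | 92.2% | 34.9% | 31.4% |

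**Simulation check** (6,000 runs per scenario):

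| Control rates by site | Power at HR 0.70, unstratified vs stratified | Type I error, unstratified vs stratified |
|---|---|---|
| 37%/34% | 79.3% vs 79.2% | 5.3% vs 5.2% |
| 50%/22% | 78.9% vs 81.1% | 4.1% vs 5.0% |
| 60%/12% | 72.4% vs 81.4% | 2.5% vs 5.5% |

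The simulated losses at HR 0.70 (about 2 and 9 points) are somewhat below the formula's 3.5 and 11. The formula takes the unstratified statistic to have unit variance, but the type I error below 5% shows that its variance is smaller. The simulation was not repeated at HR 0.651.

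**The case against.** The strongest reply is that this belongs to the Report and Analysis Plan. Section 10.9.5 defers the adjustment covariates to it, and Section 10.9.1 already promises an adjusted Cox estimate with study center first in the list. That stands against any claim that the plan ignores site altogether. A reader might infer that from the unstratified tests, but the planned adjusted estimate contradicts it. The deferral is narrower than the reply needs, however. It covers covariates for adjustment, whereas the log-rank/Wilcoxon and Fisher tests are named in the protocol with no site term, and the ranking of crude against adjusted is left open.

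The second reply is that no harm is shown. The planning rates are almost equal, and so are the entomological inoculation rates (around 90 infective bites per person per year in Korogwe, up to 100 in Kilifi; Sections 4.1.2 and 4.2.2). This stands: the larger contrasts are assumptions. They are not idle, because the two planning rates are not like for like. Kilifi's comes from active detection at 12 to 18 months, Korogwe's from passive detection at 5 to 17 months in one village. Bednet use was 16 to 28% of people in Korogwe against 70% of children aged 1 to 5 years in Kilifi at the end of 2005, although Section 5.8.1 commits the teams to optimising net use at both.

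A reader might also infer from the different seasons that the baseline hazards differ in shape, so that a site covariate would not be enough. That was not tested, since the calculations use constant hazards. Analysis time runs from 14 days after Dose 3, surveillance started anywhere from May to October 2007 (Section 1.6.4), and the stated seasons overlap from June to August. Different shapes are possible but not demonstrated.

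Finally, the shift is small beside sampling error. With 245 events the standard error of the log hazard ratio is about 2/√245 = 0.128, so a hazard ratio of 0.70 has a 95% interval of about 0.55 to 0.90. This also stands. No loss was calculated for the parasite prevalence test, and Fisher's test there is valid.

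**Conclusion.** The point holds as one of efficiency and specification. The protocol randomises by site, names tests and a crude Cox estimate that leave site out, and does not say which efficacy estimate is primary.

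The size depends wholly on how far the site risks differ. At 37%/34% the power loss is below 0.1 point and the efficacy shift about 0.01 point. With site hazards about 2.8-fold apart, the loss is about 2 to 3.5 points of power and about 1 point of efficacy. At about 7-fold apart, it is about 8 to 11 points of power and 3 to 3.5 points of efficacy. These figures rest on equal site sizes, constant hazards and a common hazard ratio.

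It would be wrong to conclude that the unstratified analysis is invalid or favours the vaccine. Its simulated type I error fell to 4.1% and 2.5% under the larger contrasts, and the crude estimate moves towards no effect.

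**What to change.** Before unblinding, state in Section 10.9.1 or the Report and Analysis Plan that:
- the primary log-rank/Wilcoxon test and Cox model are stratified by study site, with a separate baseline hazard for each site;
- this site-stratified estimate is the primary vaccine efficacy estimate;
- the other listed covariates enter a secondary adjusted estimate.

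In Section 10.9.3, replace the plain Fisher test on parasite prevalence with a Cochran-Mantel-Haenszel test stratified by site, or an exact stratified test if counts are small.

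The cost is one analysis option, with no extra data or children. If site risks turn out equal, the results are essentially unchanged.

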### 10.9.2. Total number of events analyses

For the analysis of multiple episodes (clinical malaria), a table with the frequency of children with 0, 1, 2, 3, 4 or more episodes in each group will be presented. Differences in the distribution of number of episodes will be evaluated using a Fisher exact test. The incidence of episodes (episodes/person years at risk) for each group will be presented. The significance of the group effect will be assessed using Poisson regression models with random effects including the time at risk as an off-set variable. If there is evidence of lack-of-fit to the Poisson model, alternative models will be investigated. Vaccine efficacy is defined as 1 *minus* R where R is the rate ratio of clinical episodes of the RTS,S/AS01E group versus the Control group (with 95% CI). Crude and adjusted estimates for covariates will be presented if appropriate.

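### Section 10.9.2 pairs the ordered episode-count table with an unordered Fisher exact test; a rank test on the same table is somewhat more powerful and costs nothing

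*Protocol*

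**What the plan says.** Section 10.9.2 deals with multiple clinical episodes in three steps.

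- **Table:** "a table with the frequency of children with 0, 1, 2, 3, 4 or more episodes in each group will be presented".
- **Test on that table:** "Differences in the distribution of number of episodes will be evaluated using a Fisher exact test". Nothing is said about order, scores or trend.
- **Inference on the group effect:** "The significance of the group effect will be assessed using Poisson regression models with random effects including the time at risk as an off-set variable". Alternative models follow if the Poisson fit is poor. Vaccine efficacy is 1 minus R, where "R is the rate ratio of clinical episodes of the RTS,S/AS01E group versus the Control group", with a 95% CI.

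The section serves the secondary multiple-event endpoints under two case definitions (Section 10.2) and the tertiary ones over longer periods (Section 10.3), in both the ATP and Total cohorts (Sections 10.10.1 and 10.11.1). The next section, 10.9.3, uses Fisher for a 2×2 positive/negative table and Wilcoxon for hemoglobin and parasite density.

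The only power statement, in Section 10.6.1, concerns children with any episode: "a sample size of 400 evaluable subjects per group has 90% power to detect a difference between groups". That figure refers to a two-sided Fisher test at the 5% level. The protocol gives no power, count distribution or dispersion for the 2×5 table.

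**The concern.** The number of episodes is an ordered outcome, and the clinical question has a direction: do vaccinees have fewer? A Fisher exact test on a 2×5 table (the Fisher-Freeman-Halton test) looks for any difference in the distribution. It would give the same p-value if the category labels were shuffled, so some of its sensitivity goes to patterns that nobody expects.

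The protocol names this as a test and does not call it descriptive, so a p-value will stand next to the Poisson rate ratio for the same endpoint. At stake is how readable that pair of results is: a non-significant Fisher p-value could sit beside a significant rate ratio.

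**Working it through.** **1. Reproduce the plan's own figure.** Inputs from Section 10.6.1: 400 per group, 36% versus 25.2% with any episode, two-sided 5% Fisher test. Exact enumeration for the 2×2 table gives 90.2% power, so the stated 90% holds. Expected children affected: 400 × 0.36 + 400 × 0.252 = 244.8, matching the trigger of about 245.

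**2. Build counts that agree with the 36%.** The protocol gives no count model, so these are assumptions: Poisson, or negative binomial with dispersion k = 2, 1 or 0.5. Setting the zero term to 1 − p gives the mean m:

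- Poisson: m = −ln(1 − p)
- Negative binomial: m = k[(1 − p)^(−1/k) − 1]

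Control means at p = 0.36 are 0.446 (Poisson), 0.500 (k = 2), 0.562 (k = 1) and 0.721 (k = 0.5).

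**3. Two readings of 30% efficacy.**

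- **(a) Attack-rate reading, as in Section 10.6.1:** 25.2% of vaccinees affected. With Poisson counts the vaccine mean is −ln(0.748) = 0.290, a rate ratio of 0.290/0.446 = 0.65.
- **(b) Rate-ratio reading, the measure in Section 10.9.2:** vaccine mean = 0.70 × control mean. With Poisson counts this is 0.312, so 1 − exp(−0.312) = 26.8% are affected. This is a weaker effect than (a).

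**4. Simulate.** 4,000 trials per scenario, 400 per group, two-sided 5%. Fisher-Freeman-Halton p-values come from 2,000 conditional Monte Carlo tables; the Wilcoxon test is tie-corrected. A robust Poisson rate test stands in for the protocol's random-effects model. Some runs apply a 28-day not-at-risk period after each episode (Section 10.9.4, artemether/lumefantrine) within 122 days. The loss column is Wilcoxon minus Fisher, in points.

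| Reading | k | 28-day gap | Fisher 2×5 | Wilcoxon | Loss | Poisson rate test |
|---|---|---|---|---|---|---|
| (a) | Poisson | no | 88.2% | 93.3% | 5.1 | 95.1% |
| (a) | Poisson | yes | 89.1% | 93.8% | 4.7 | 95.0% |
| (a) | 2 | no | 88.6% | 94.6% | 6.0 | 96.5% |
| (a) | 2 | yes | 89.7% | 93.6% | 3.9 | 95.4% |
| (a) | 1 | no | 90.2% | 94.8% | 4.6 | 97.8% |
| (a) | 1 | yes | 89.4% | 93.9% | 4.5 | 96.2% |
| (a) | 0.5 | no | 94.0% | 96.6% | 2.6 | 99.4% |
| (a) | 0.5 | yes | 92.2% | 95.4% | 3.2 | 98.0% |
| (b) | Poisson | no | 74.1% | 83.6% | 9.5 | 87.2% |
| (b) | Poisson | yes | 74.2% | 81.7% | 7.5 | 84.2% |
| (b) | 2 | no | 66.7% | 78.7% | 12.0 | 84.4% |
| (b) | 2 | yes | 68.2% | 78.2% | 10.0 | 81.4% |
| (b) | 1 | no | 60.1% | 72.0% | 11.9 | 80.7% |
| (b) | 1 | yes | 59.2% | 70.6% | 11.4 | 75.9% |
| (b) | 0.5 | no | 48.8% | 58.7% | 9.9 | 74.4% |
| (b) | 0.5 | yes | 47.4% | 57.7% | 10.3 | 66.5% |

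Simulation error is about 0.5 to 1 point per power estimate. Separate runs gave losses as low as 1.7 points (94.1% versus 95.8%) and as high as about 7 in (a), and up to about 14 in (b). Hence the ranges of roughly 2–7 and 7.5–14.

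**5. Disagreement between the two p-values.** A non-significant Fisher test beside a significant rate test occurred in about 8 to 24% of simulated trials, depending on the scenario.

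**The case against.** The strongest reply is that the Fisher test governs nothing. It accompanies a frequency table; the next sentences give the significance of the group effect, and vaccine efficacy with its interval, to a Poisson model that uses both the counts and the time at risk. This stands. A reader might infer from the Fisher sentence that the multiple-episode endpoint is decided by a weak test, or that its efficacy conclusion is at risk. Section 10.9.2 does not support that.

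A reader might also want one headline figure, such as a loss of about 12 points. The documents do not support that either. It needs a rate ratio of 0.70 and moderate overdispersion (k of 1 to 2), neither of which the protocol states as a planning value. At 36% versus 25.2%, Fisher power on the 2×5 table is still about 87 to 94%. The rate-ratio reading is nevertheless relevant: Section 10.9.2 defines efficacy that way, and Section 1.4 reports 27.4% efficacy against multiple attacks over six months in the earlier Mozambican trial, a rate ratio of 1 − 0.274 = 0.726.

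Further, an omnibus test is valid at its nominal level and does answer a question about any difference in distribution. True, but the order of the counts is known in advance and the expected effect has a direction, so ignoring the order gains nothing here. Finally, a rank test also ignores time at risk and can also disagree with the Poisson result. That is correct: it makes disagreement less frequent without removing it, which is why the Poisson model should stay in charge.

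**Conclusion.** The point holds in a limited form. As worded, the test beside the 0/1/2/3/4+ table is unordered and is less powerful than a rank test on the same data in every scenario tried. The size is a range: roughly 2–7 points at the protocol's planning rates and roughly 7.5–14 points at a rate ratio of 0.70. It rests on assumed Poisson or negative binomial counts, 400 children per group and equal planned follow-up.

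The Poisson-based efficacy estimate and group-effect test are unaffected. The stand-in rate test equalled or exceeded the rank test throughout (95–99% in (a), 67–87% in (b)). The primary endpoint and sample size are untouched. What remains is a weaker secondary p-value that may disagree with the rate ratio: a minor matter and a free improvement.

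**What to change.** In Section 10.9.2, keep the frequency table and replace the Fisher test with a Wilcoxon rank-sum test on the ordered episode counts, corrected for ties, or a trend test with scores 0 to 4. Add one sentence saying that this p-value is supportive, and that the random-effects Poisson model with the time-at-risk offset remains the test of the group effect and the source of vaccine efficacy.

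The cost is one line of text and one line of code. Data collection, sample size, conduct and the efficacy estimate do not change, and Wilcoxon tests are already used in Section 10.9.3. Settle the choice before counts by group are seen.
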